## Abstract

**Introduction:**

Within the UK there are 33 deaths every day from prostate cancer, second only to lung cancer as the most common cause of cancer death in males in the UK. Of the 55 000 new cases each year, up to 50% of these patients will receive radiotherapy either alone or after prostatectomy. Although there have been significant improvements in the accuracy of radiotherapy delivery leading to better tumour targeting and a reduction in dose to normal tissues, significant permanent genito-urinary or gastrointestinal-related side effects are all too common. With nearly 80% of patients with prostate cancer surviving for 10 years or more, minimising life-limiting radiation damage to normal tissues is vitally important. However, at present, it is not possible to identify which patients will suffer a poorer outcome after radiotherapy. The aim of this study, improving radiotherapy in **PROS**tate cancer using **E**le**C**tronic population-based health**CA**re data (PROSECCA), is to do this by using the existing information in a patient’s digital healthcare record. By linking primary, secondary and tertiary clinical data, including digital image information, with radiotherapy treatment plans and outcome data, the PROSECCA study will identify de novo predictive biomarkers of radiation response and provide clinicians with a tool to individualise a radiotherapy dose and plan to maximise cure and minimise toxicity.

**Methods and analysis:**

The PROSECCA study is a large multidisciplinary project, the purpose of which is to analyse healthcare records from up to 15 000 patients with prostate cancer who underwent radiotherapy in the treatment of their cancer in Scotland between 2010 and 2022. Through the linkage of data obtained specifically for radiotherapy and data held within each patient’s unique electronic health record (EHR), the factors that indicate why some patients have a poor response to treatment, or an increased risk of side effects from radiation, will be identified. This will be made possible by the use of artificial intelligence and machine learning (AL/ML), which will help to identify at-risk patients earlier and allow adaptation of their treatment accordingly.

**Ethics and dissemination:**

The study is being conducted in accordance with the ethical principles set out in the Declaration of Helsinki and Good Clinical Practice that respects and protects the rights, and maintains confidentiality, of all trial participants. The study protocol (V.1.0) was reviewed by the South Central Oxford A Research Ethics Committee (REC) on 13 December 2021 and received a favourable opinion subject to each National Health Service (NHS) organisation confirming permission for patients treated within their area. Approval for the use of unconsented healthcare record data for patients included in the study and treated at one of the five Scottish Cancer Centres required an application to the NHS Scotland Public Benefit and Privacy Panel for Health and Social Care (HSC-PBPP). Full approval from the HSC-PBPP panel was received on 1 July 2024, which covered the use of pseudoanonymised EHR data for all patients participating in the study. The study is publicly listed on the NHS Health Research Authority site, with IRAS ID 306245 and REC reference 21/SC/0402. Dissemination of the study findings will take place through field-leading cancer, radiation oncology and medical physics journals. All manuscripts will be approved by the main study team and authorship determined by mutual agreement.

**Trial registration number:**

NCT06714630.

STRENGTHS AND LIMITATIONS OF THIS STUDYThe PROSECCA study will include EHR data that are not currently taken into account in radiotherapy.The linkage of radiotherapy treatment planning data with mass digitalised healthcare records will create a range of longitudinal phenotype information for patients with prostate cancer treated in Scotland.All digitalised healthcare records held by Public Health Scotland (PHS) adhere to international coding standards accessible by a unique patient identifier.The cohort is currently restricted to patients treated in Scotland; however, plans are in place to establish performance on an independent cohort of patients treated across the UK.

## Introduction

 Between 2017 and 2019, prostate cancer accounted for 14% of all cancer deaths in the UK. This equates to over 12 000 men making it the second most common cause of cancer death in males.^1^ In the same period, over 55 000 men were diagnosed with prostate cancer, nearly half of whom received external beam radiotherapy as part of their treatment. In the majority of cases, radiotherapy is given as a curative treatment because of its effectiveness at destroying cancerous cells deep within the body. However, this comes at the cost of potentially damaging healthy, or normal, tissues close to the target.^1 2^

Current National Institute for Health and Care Excellence (NICE) guidelines recommend that prostate cancer is classified into three groups, low, intermediate and high, based on the risk of the disease spreading.^3^ In broad alignment with National Comprehensive Cancer Network (NCCN) guidelines, these groups are defined here as: low risk=prostate specific antigen (PSA)<10, Gleason Score≤6, T1-2a; intermediate risk=PSA 10–20, Gleason Score=7, or T2b-c; high risk=PSA>20, Gleason Score≥8, or T3-4.^4 5^ Tumour stage is based on digital rectal examination and the addition of either transrectal ultrasound, computerised tomographic (CT) and/or a magnetic resonance (MR) imaging. In Scotland, prostate biopsy is recommended for patients in the following categories: <50 years and PSA>3; 50–60 years and PSA>4; >60 years and PSA>5.

In managing patients with localised disease, the most common treatment options are radical prostatectomy and external beam radiotherapy, both of which are currently held at therapeutic equipoise.^6^,^9^ The focus of the PROSECCA study is on external beam radiotherapy where a linear accelerator has been used to deliver precise radiation doses to a predefined target volume over a number of days. Typically, doses in the range of 2–3 Gy are given each day, or fraction of treatment, over several weeks.^10^ More recently, hypofractionation treatments, which deliver much higher doses in fewer fractions, have been shown to be safe and effective for low and intermediate risk patients.^11^,^14^ However, irrespective of dose and fractionation schedule, life-limiting side effects from radiotherapy are common.^2 9^ The key to reducing side effects is to personalise an individual’s radiotherapy treatment. While there has been progress on doing this based on tumour biology as shown in the landmark study, validating predictive models and biomarkers of radiotherapy toxicity to reduce side-effects and improve quality-of-life in cancer survivors (REQUITE), such approaches, which require patients to provide biological samples, are expensive and not suitable for rolling out into everyday practice across the National Health Service (NHS).^15 16^ New approaches are required and this is the motivation for this study, improving radiotherapy in **PROS**tate cancer using **E**le**C**tronic population-based health**CA**re data (PROSECCA), which will use linked digital healthcare data acquired across a whole population to predict clinical outcomes for patients with prostate cancer undergoing radiotherapy. Currently, this is not done and little or no account is taken of the vast array of data that are available for each patient from their electronic health record (EHR), the extensive digital imaging data collected at diagnosis and during treatment, and during a course of radiotherapy.

The PROSECCA study aims to formalise an approach for identifying factors in a patient’s EHR that are reliable biomarkers of radiation-induced injury. In addition, the project will establish a centralised database containing radiotherapy data and linked healthcare records from patients with cancer treated in Scotland. In order to deliver on these goals, the project has a number of objectives:

### Nationwide radiotherapy-specific data and linked digital healthcare records

The establishment of a nationwide database containing radiotherapy-specific data and linked healthcare records from patients with cancer treated in Scotland will serve as the test bed for the project. There is no such resource of this nature and scale currently available in the radiotherapy cancer community. The ability to link population-based differences in, for example, dose to tumour and normal tissue; fractionation schedules; treatment machines; cancer stage and grade; planning techniques to specific healthcare record information will be a significant outcome.

### Prediction of a patient’s risk of radiation toxicity and tumour control

Using the linked dataset, predictive factors will be established indicating that a patient may have a poor response to treatment, including the increased risk of normal tissue toxicity. This information will be available both (1) prior to treatment and (2) during the course of treatment.Medium (5 year) and long (10 year) estimates of three clinically significant endpoints: (1) PSA relapse-free survival, (2) overall survival and (3) radiotherapy toxicity.To ensure maximum clinical impact, a software application, available to clinicians in the clinic, will be developed to use these predictive factors to identify (1) the most appropriate form of therapy, (2) the most appropriate dose and fractionation schedule and (3) the optimal time and how best to adapt treatment.To establish a pathway and methodology showing how the approach developed in PROSECCA can be applied to other tumour sites (eg, lung and head and neck cancer), thereby benefiting a much larger number of patients treated with radiotherapy.

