**Figure 3 F3:**
[figure not shown]
Map showing the location of the five Scottish Cancer Centres and in brackets the number of clinical linear accelerators at each location.

**Table 1 T1:** Preliminary estimates of the number of events for the three main endpoints of interest, PSA relapse-free survival, overall survival and radiotherapy toxicity as defined from all sources.

Endpoint of interest	Approach used to estimate events	Events
PSA relapse-free survival	5-year endpoint, 10% event rate based on the trial, a randomised phase III multi-centre trial of Conventional or Hypofractionated High dose Intensity modulated radiotherapy for Prostate cancer, (CHHiP) ^46^ Sample size of 11 250 based on 75% attrition in this data (75% of 15 000)	1125
Overall survival	10-year endpoint, 29% event rate based the trial, a Randomised controlled Trial of high dose versus standard dose conformal radiotherapy for localised prostate cancer, (RT01)^11 46 49^ Sample size of 7500 based on 50% attrition in this data (50% of 15 000)	2175
Radiotherapy toxicity (all sources)	5-year endpoint, 12% event rate for ≥ grade 2 based on CHIIP trial high grade group^11 46 49^ Sample size of 10 000 based on much higher attrition of 60% attrition for this endpoint of interest (60% of 25 000=10 000 followed by 12% of 10 000)	1200

Estimates were based on data from NHS ISD, Scotland, Prostate Cancer Incidence.

PSA, prostate specific antigen.

Each of the five Scottish cancer centres involved in the study uses the same commercial database for storing information on patients receiving radiotherapy for prostate cancer. This database, known as ARIA, is supplied by Varian Medical Systems^20^ and is used to maintain a complete independent record of a patient’s treatment, which is required by law under the Ionising Radiation (Medical Exposure) Regulations 2017 .^21^ Separately, Public Health Scotland (PHS), Scotland’s national public health body, holds health and social care data for the entire Scottish population (5.4 million) as far back as the 1970s. Since this time, every NHS patient treated in Scotland has been allocated a unique identifier at birth, or on registering with Scottish healthcare services. This 10-digit numeric code, known as the Community Health Index number (CHI), is the primary mechanism for patient identification for every healthcare episode that happens in Scotland, making it straightforward to access and find information about an individual patient.

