10	SBoSP	Scottish Bowel Screening Programme	25
11	SRR	Scottish Renal Registry	17
12	SHFA	Scottish Hip Fracture Audit	17
13	PDS	Dementia postdiagnostic support	10
14	DAISy	Drug and Alcohol Information System	12
15	SDMD, SMR25a, SMR25b	The Scottish Drug Misuse Database	11
16	WT	Waiting Times	7
17	SCS	Smoking Cessation Services	14
18	MS	Multiple Sclerosis	6
19	TRAK	Healthcare Information System	2
20	SPIDER	Streptococcus Pneumonia surveillance	3

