### Study objectives

The primary objectives of the PROSECCA study are to use advanced artificial intelligence and machine learning (AI/ML) techniques to analyse the EHRs of patients with prostate cancer who underwent radiotherapy in the treatment of their cancer and to establish what factors indicate that a patient may have a poor response to treatment, or an increased risk of side effects from their treatment. The secondary objectives are to use these factors to build predictive models that identify these patients much earlier than is currently possible.

Figure 4 summarises the methodological approach of PROSECCA and the key parameters/features that will be used as input to different AI/ML models. With such an extensive dataset, the majority of which has not been analysed in any way, the preliminary phase of the study will use AI/ML frameworks already proven to work well in other big-data applications (eg, multimodal deep learning models, pretrained deep learning models and ensemble approaches). These will be adjusted to estimate biochemical relapse-free survival, overall survival and risk of toxicity from these data. Specifically, this will be approached by developing a number of ML models.

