#### Multimodality deep learning models

Efficiently combining multimodality data within deep learning frameworks is challenging. The planned initial approach will involve building convolutional neural networks (CNNs) and vision transformers for imaging data and using other approaches for radiotherapy and clinical features, such as recurrent neural networks (RNNs).^23^ The output from these will be concatenated and passed to densely connected layers for classification. Labelled data will be available from: radiotherapy planning, medical imaging and EHR information (figure 4).

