#### Ensemble approaches/classical machine learning models

It is anticipated that the final classification will benefit from an ensemble approach using different AI/ML models to optimise classification. For example, decision trees, support vector machines, nearest neighbour and naive Bayes’ classifiers, all of which have been used extensively in previous radiotherapy and cancer classification problems.^25^,^31^

Serving as input data to these models will be unique information, or features, extracted from radiotherapy, imaging and EHR data. Currently, it is estimated that there will be, per time point of interest, more than 500 features of interest comprising:

Radiotherapy planning features (n=20+ features).Including, but not limited to, dose to prostate and organs at risk, organ volume, number of fractions, delivery technique, dose calculation algorithm.Image analysis/radiomic features (n=150+ features).Including texture/radiomics analysis based on low-level and high-level feature analysis, features based on organ shape and position, features derived from other approaches such as Fourier analysis and wavelet analysis.Clinical/patient-specific features from EHRs (n=431 features at multiple timepoints).Including PSA, staging, Gleason score, age, smoking history, comorbidities including prescription medications via ICD-10 indicative of diseases such as cardiovascular and diabetes.

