#### Outcome measures

The primary outcome measures of the PROSECCA study are to establish what a patient’s probability of relapse-free survival, metastatic-free survival, cause-specific and overall survival will be when data from their EHR is combined with radiotherapy-specific parameters.

Secondary outcome measures include imaging-derived biomarkers and the independent and codependent predictive power of variables held within each patient’s EHR (online supplemental table 4) for prediction of primary outcomes.

Research and technical-scientific secondary outcomes include the curation of a population-based radiotherapy database containing imaging, dose and radiotherapy planning data and linked healthcare data from the national PHS archive. This also includes the establishment of a secure virtual environment, with high-performance computing capability, for rapid model development and outputs on the performance of a range of AI/ML models in predicting primary outcomes. Once established, this resource will also be used for future discovery research as well as validation of findings made by other researchers.

Patient-specific secondary outcomes will be in the form of a testbed for investigating the relationship between biochemical failure and radiotherapy-specific parameters such as dose, fractionation and planning techniques. This will also include how to personalise, or adapt, a patient’s course of radiotherapy by suggesting: the best form of therapy; the most appropriate dose and fractionation schedule; the optimal time to adapt; and the best mechanism for assessing any proposed personalised treatment. This will be available through an easy-to-use app.

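### The classifiers named for 5- and 10-year toxicity do not separate death before toxicity from being alive without it, and no way of coding those deaths serves both stated aims

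*Protocol article*

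**What the plan says.** The section on predicting toxicity and tumour control commits to "Medium (5 year) and long (10 year) estimates of three clinically significant endpoints: (1) PSA relapse-free survival, (2) overall survival and (3) radiotherapy toxicity". Study objectives says of existing AI frameworks that "These will be adjusted to estimate biochemical relapse-free survival, overall survival and risk of toxicity from these data", and then introduces the specific models for the purpose.

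- For the deep learning models: "The output from these will be concatenated and passed to densely connected layers for classification".
- The ensemble section anticipates that "the final classification will benefit from an ensemble approach using different AI/ML models to optimise classification". Its examples are decision trees, support vector machines, nearest neighbour and naive Bayes.

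The text describes no time-to-event or competing-event model for toxicity.

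Table 1 plans overall survival as "10-year endpoint, 29% event rate based the trial" and toxicity as "5-year endpoint, 12% event rate for ≥ grade 2". It gives no 10-year toxicity rate. The Discussion puts 10-year survival at 80%. The legend of Figure 2 says the study will examine whether statins and antihypertensives protect against toxicity, and the prediction section plans a clinician application built on the factors found. Table 2 lists linked national death records (14 variables). It also lists stroke, renal and hip-fracture registers and "Dementia postdiagnostic support".

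**The concern.** A man who dies free of toxicity can no longer develop it. A fixed-horizon classifier must still give him a label or leave him out. This is not a matter of short follow-up: it remains if every man is observed for the full 10 years.

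The article wants two things from the same model: factors that can be read as protective or harmful, and individual probabilities at 5 and 10 years. Each coding damages at least one of them.

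- **Labelled as no toxicity.** The probability is a valid risk in the presence of death. A condition that shortens life looks protective, because it leaves less time for toxicity to appear.
- **Dropped.** The probability is too high, and the same condition looks harmful.
- **Censored, in a hazard model.** Factor effects are the cause-specific ones, but the risk shown to the patient is too high.

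The direction of a spurious association therefore turns on the coding. Calibration in the external data would not reveal the problem if deaths were coded the same way there.

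**Working it through.** **Plan's own figures.** Table 1 reproduces: 7500 × 0.29 = 2175 deaths and 10 000 × 0.12 = 1200 toxicity events. The 29% is a 10-year rate and the 12% a 5-year rate, both borrowed from outside trials.

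**Assumptions (not in the article).** Hazards are constant and independent, the 12% is read as the 5-year risk with deaths censored, and the same hazard continues to year 10.

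- Toxicity hazard: λt = −ln(0.88)/5 = 0.0256 per year.
- Death hazard: λd = −ln(0.71)/10 = 0.0342 per year at 29% mortality; −ln(0.80)/10 = 0.0223 at 20%.

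**Formulas at time t.**

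- Cumulative incidence: CIF = λt/(λt+λd) × (1 − exp(−(λt+λd)t)).
- Deaths censored: 1 − exp(−λt·t).
- Toxicity-free deaths dropped: CIF/(CIF + exp(−(λt+λd)t)).

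**At 10 years, 29% mortality.** Alive and toxicity-free: 0.88² × 0.71 = 0.5498. CIF = 0.4274 × 0.4502 = 19.2%. Censored: 1 − 0.88² = 22.6%. Dropped: 0.1924/(0.1924 + 0.5498) = 25.9%.

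| 10-year mortality | Horizon | CIF | Censored | Dropped | Censored vs CIF |
|---|---|---|---|---|---|
| 29% | 5 years | 11.05% | 12.0% | 13.0% | 9% too high |
| 29% | 10 years | 19.2% | 22.6% | 25.9% | 17% too high |
| 20% | 5 years | 11.4% | 12.0% | 12.6% | 6% too high |
| 20% | 10 years | 20.3% | 22.6% | 24.7% | 11% too high |

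**Direction of the false association.** Take a condition with no effect on toxicity, held by 20% of men (assumed), that multiplies the death hazard by 2, 3 or 5 (assumed). Overall 10-year mortality is held at 29%.

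For a ratio of 3, the 10-year CIF is 19.99% without the condition and 15.96% with it.

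- Deaths labelled as no toxicity: (0.1596/0.8404)/(0.1999/0.8001) = 0.76.
- Deaths dropped: risks of 25.1% and 30.9%, an odds ratio of 1.34.
- Deaths censored: 22.6% in both groups.

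| Death hazard ratio | 10-year mortality, without / with | Odds ratio, deaths labelled no toxicity | Odds ratio, deaths dropped |
|---|---|---|---|
| 2 | 25.2% / 44.1% | 0.85 | 1.18 |
| 3 | 22.8% / 53.9% | 0.76 | 1.34 |
| 5 | 19.6% / 66.5% | 0.64 | 1.65 |

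At 5 years, with deaths labelled as no toxicity, the odds ratios are 0.93, 0.87 and 0.80.

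**Are markers of mortality among the inputs?** Yes. Stroke 33 + renal 17 + hip fracture 17 + dementia 10 = 77 of the 431 features in Table 2. This counts variables, not men.

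**The case against.** The strongest objection is that the article nowhere says toxicity is coded yes/no, or that death will be ignored. Labelling and censoring rules are commonly left to an analysis plan, which is not shown here. The model sections are worded as initial and anticipated, and the frameworks are to be adjusted to the endpoints. Death records are linked, and overall survival is an endpoint. Figure 4 is not visible, and its legend expands LASSO, which could be fitted to a hazard. All of this stands against reading the article as giving death no role. What remains is that it does name a model family for a fixed-horizon outcome, and that family in standard form has no place for a competing event.

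A reader might also infer that life-shortening conditions would look protective and individual risks would be inflated at the same time. No single coding considered here does both, and the article selects none of them.

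The size can fairly be challenged too. No 10-year toxicity rate is given, so the 10-year figures are extrapolated. Mortality may be below 29%: the Discussion implies about 20%, and gives under 5% for low- and intermediate-risk men without stating the cause. If that 5% were all-cause, the 10-year CIF would be 0.2557/(0.2557 + 0.0513) × (1 − 0.7744 × 0.95) = 22.0% against 22.6% censored, which is negligible. The condition's prevalence and death hazard ratios are also assumed.

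Finally, the primary outcomes cover "probability of relapse-free survival, metastatic-free survival, cause-specific and overall survival will be when data from their EHR is combined". Naming cause-specific survival there is not an error, and preferring another summary would be a matter of taste.

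**Conclusion.** The point holds as a mismatch between the named methods and the two uses of the toxicity endpoint, chiefly at the 10-year horizon. It does not show that the study will ignore death. With 29% mortality, 10-year toxicity is 19.2% as cumulative incidence. Censoring raises this to 22.6% (17% relative) and dropping deaths to 25.9% (35% relative). With 20% mortality, censoring overstates by about 11%. At 5 years the effect is modest. A condition unrelated to toxicity can show a 10-year odds ratio below or above 1 depending only on the coding. These sizes are illustrations under constant, independent hazards and an extrapolated 5-year rate. The qualitative conclusion needs only that an appreciable share of men die toxicity-free and that mortality differs between patient groups.

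**What to change.** State that death before toxicity is a competing event, and give each aim its own estimand.

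1. To identify factors, model the cause-specific hazard of toxicity, so that early death is not read as protection.
2. For the 5- and 10-year patient probabilities, predict the cumulative incidence of toxicity with death as the competing event, using a competing-risk or multi-state model in place of a plain classifier.
3. Assess calibration against Aalen-Johansen estimates, in the Scottish data and in the external validation.

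The linked national death records supply what is needed, so no new data or patients are required. The cost is some extra modelling and a few sentences of text. Predicted 10-year risks will come out lower than under censoring or exclusion.

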### Protocol

#### Patient selection

Patients with prostate cancer who have received external beam radiotherapy with radical intent are eligible for inclusion in the PROSECCA study. Patients must have had PSA recorded at regular intervals after radiotherapy, a radiotherapy planning CT and corresponding radiotherapy and healthcare data available.

Patients who have received external beam radiotherapy as part of a palliative treatment schedule are not eligible for inclusion in the study, as well as those with no PSA information and follow-up healthcare and imaging data.

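### An external-beam-only cohort analysed with outcome-prediction models does not support an app that recommends form of therapy, dose and fractionation, or time to adapt

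*Protocol article*

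**What the plan says.** The objectives in the Introduction (under *Prediction of a patient's risk of radiation toxicity and tumour control*) include a clinic application, built on the predictive factors found in the study, whose task is given as "identify (1) the most appropriate form of therapy, (2) the most appropriate dose and fractionation schedule and (3) the optimal time", together with the manner of adaptation. *Outcome measures* lists much the same as a patient-specific secondary outcome: "the best form of therapy; the most appropriate dose and fractionation schedule; the optimal time to adapt". There the words sit in a sentence about personalising a course of radiotherapy. The last paragraph of the Discussion repeats the aim as longer-term impact.

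*Patient selection* sets the cohort: "Patients with prostate cancer who have received external beam radiotherapy with radical intent are eligible for inclusion". The Introduction says "The focus of the PROSECCA study is on external beam radiotherapy", having just named the main alternative: "the most common treatment options are radical prostatectomy and external beam radiotherapy, both of which are currently held at therapeutic equipoise".

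The analysis is described under *Study objectives* and the model subsections. Networks and classifiers are trained to predict relapse-free survival, overall survival and toxicity, with dose, number of fractions and delivery technique among the input features. *External validation* will examine calibration and behaviour on unseen data from a linked UK prospective study of long-term radiotherapy side effects.

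**The concern.** Predicting what will happen to a man under the treatment he is given is one question. Deciding which treatment would serve him best is another, because it needs his expected outcome under at least two options. The article moves from the first to the second without an intermediate step.

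Two separate difficulties follow. For modality, the cohort contains no one on an alternative. For dose, fractionation and timing, the alternatives are present, but changing an input to a prediction model does not reproduce the effect of changing the treatment if schedule is related to prognosis. The Introduction makes such a relation plausible: "More recently, hypofractionation treatments, which deliver much higher doses in fewer fractions, have been shown to be safe and effective", and it goes on to specify low and intermediate risk. At stake is whether clinicians would receive associations, possibly confounded by indication, in the form of treatment advice.

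**Working it through.** **1. What the article sizes.** Table 1 gives event rate × retained sample:
- PSA relapse-free survival: 0.10 × (0.75 × 15 000) = 1125
- Overall survival: 0.29 × (0.50 × 15 000) = 2175
- Toxicity: 0.12 × (0.40 × 25 000) = 1200

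All three reproduce, reading the toxicity sample of 10 000 as the 40% retained. They count events for outcome prediction. No treatment contrast, effect size or allocation is stated.

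**2. Form of therapy read as modality.** The information on a log hazard ratio between two groups is about d × p × (1 − p), with d events and share p in one group. By eligibility the share without external beam radiotherapy is p = 0:
- 1125 × 0 × 1 = 0

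This holds at any d. Men irradiated after surgery do not change it. The Abstract says "up to 50% of these patients will receive radiotherapy either alone or after prostatectomy", and all of these men are irradiated.

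**3. Dose and fractionation.** These vary and are captured. The objectives list "dose to tumour and normal tissue; fractionation schedules; treatment machines; cancer stage and grade; planning techniques" among the differences to be linked with health records. The article does not give the share on each schedule, so I assume p from 5% to 50%, a hazard ratio of 0.8 and two-sided alpha of 0.05. Power = Φ(|ln 0.8| × √(d p(1 − p)) − 1.96), with d = 1125:

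| p (assumed) | d p(1 − p) | Power |
|---|---|---|
| 0.05 | 53.4 | 37% |
| 0.10 | 101.3 | 61% |
| 0.30 | 236.3 | 93% |
| 0.50 | 281.3 | 96% |

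A contrast can therefore be computed, often with good precision. The open question is bias.

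**4. Possible size of the bias.** Suppose schedule has no effect, and a risk factor that is not adjusted for has risk ratio RR and prevalence p₁ on one schedule and p₀ on the other. The apparent risk ratio is [1 + p₁(RR − 1)] / [1 + p₀(RR − 1)]. All values here are assumed:
- RR 1.5, 60% v 40%: 1.30/1.20 = 1.08
- RR 2, 70% v 30%: 1.70/1.30 = 1.31
- RR 3, 80% v 20%: 2.60/1.40 = 1.86

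**5. Why validation does not settle it.** Calibration compares predicted with observed outcome under the treatment each man received. If schedule and prognosis are linked in the same way in the validation data, a model that has absorbed that link will still calibrate well. The check cannot separate the effect of schedule from its association with risk.

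**6. Follow-up, for illustration only.** With treatment from 2010 to 2022, uniform accrual, and February 2025 (first access to linked data) taken as cut-off:
- 10 years: (2025.1 − 10 − 2010)/13 = 39%, or /12 = 42.5%
- 5 years: (2025.1 − 5 − 2010)/13 = 78%, or /12 = 84%

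**The case against.** The case on the other side has real force, and several stronger readings fail because of it.

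- *A reader might infer that none of the promised comparisons can be estimated.* For dose, fractionation and timing that is wrong. They vary across five centres and the 2010 to 2022 treatment years and are recorded, and their relation to biochemical failure is a stated outcome. Confounding makes a contrast dependent on assumptions; it does not make it inestimable. Several obvious confounders (PSA, stage, Gleason score, age, comorbidity) are among the listed features.
- *A reader might infer that the app will choose between surgery and radiotherapy.* No section says so. In *Outcome measures* the phrase belongs to a sentence about a course of radiotherapy, so technique is a fair reading. The objective and the Discussion are looser, and the term is nowhere defined, so the ambiguity stands.
- *A reader might infer that schedule was allocated by risk group, centre and era.* The Introduction reports published evidence on hypofractionation, not Scottish practice. Confounding by indication is plausible, not documented.
- *A reader might infer that newer schedules lack 10-year data.* No adoption dates or data cut-off are given. The 39–43% says nothing about particular schedules, and 5-year endpoints are better covered.
- *A reader might infer that unassessed advice would go straight to clinic.* The article commits to external validation and TRIPOD reporting, speaks of a testbed, and acknowledges barriers to clinical use.

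The article is also condensed, so an adjustment method may sit in a full protocol or analysis plan; its absence here is not the point. Such a document could not supply patients whom eligibility excludes. Nor would it alter the published wording, which goes directly from predictive factors to a recommended schedule.

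**Conclusion.** The point holds in two parts.

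First, the stated output on form of therapy does not fit the eligibility rule if it means modality: the information is exactly zero. This depends on that reading. If technique within external beam radiotherapy is meant, the cohort does hold variation and the defect is one of wording.

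Second, recommendations on dose, fractionation and timing do not follow from models that predict outcome given the treatment received, however well those models calibrate. The contrasts can be estimated under no unmeasured confounding and adequate overlap between schedules, but the step described does not rest on such an analysis. The possible distortion, an apparent risk ratio of 1.08 to 1.86 with no true effect, comes from assumed inputs. It shows scale and is not an estimate for this cohort.

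The change should be made, because it alters what the study can claim to conclude. The prediction aims themselves are not undermined.

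**What to change.** 1. Reconcile the app objective in the Introduction, the patient-specific secondary outcome in *Outcome measures* and the last paragraph of the Discussion with *Patient selection*.
2. Define *form of therapy* as options within external beam radiotherapy, or remove it as an output of this cohort.
3. State the tool's output as predicted outcome under the planned radiotherapy.
4. Present any comparison of dose, fractionation or timing only from a separate, pre-stated analysis that adjusts for treatment selection (for example risk group, comorbidity, centre and calendar year), confined to where schedules overlap and labelled hypothesis-generating. An emulated target trial starting at radiotherapy is one suitable form.

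The cost is narrower claims, a less ambitious app in this phase, and one added analysis. On the article's account, no new data collection is needed, since the treatment variables and many likely confounders are already to be linked.
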